#### 7.1.3. Safety Analysis Set (SAS)

SAS includes patients who received at least one Shingrix^®^ dose.

### 7.2. Primary Endpoint

The number and proportion of patients positive for anti-gE antibodies at 4 weeks after the second Shingrix^®^ dose will be summarized for each group.

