## Abstract

**Background**: Janus kinase (JAK) inhibitors have emerged as a new class of disease-modifying anti-rheumatic drugs in the treatment of rheumatoid arthritis (RA). However, herpes zoster is one of the common adverse events of JAK inhibitors, including upadacitinib, which is especially high in Japanese patients with RA compared to those from Western countries. Recombinant zoster vaccine (Shingrix^®^) is an adjuvanted subunit vaccine containing varicella-zoster virus (VZV) glycoprotein E (gE) that is effective in adults over 50 years of age. Despite this, no studies have examined its immunogenicity in Japanese patients receiving upadacitinib. Therefore, this study aims to examine the effectiveness of the recombinant zoster vaccine in Japanese patients with RA receiving upadacitinib. **Methods**: This is a single-center, exploratory, interventional, open-label, parallel triple-arm, prospective study. A total of 69 patients (23 in each group) aged 50 years or over and treated with a stable dose of methotrexate (MTX) monotherapy (6–12 mg/week), upadacitinib monotherapy (15 mg/day), or MTX (6–12 mg/week) + upadacitinib 15 mg/day (combination) for at least 1 month prior to study entry will be included. Moreover, all three groups will receive two intramuscular injections of the recombinant zoster vaccine at 8-week intervals. The primary endpoint is the proportion of positive anti-gE antibodies 4 weeks after the second injection. Secondary endpoints include RA disease activity, positive gE-specific CD4+ T-cells, and VZV-specific antibodies at indicated time points. Data on outcome measures will be collected at baseline and at 4, 8, 12, and 20 weeks. Endpoints will be summarized using descriptive statistics from baseline therapy, and results will be compared in an exploratory manner. **Discussion**: Despite the limited generalizability due to its design as a single-center, single-ethnic study, small sample size, and short observation period, this study provides evidence on the effectiveness and tolerability of recombinant zoster vaccine in Japanese patients with RA receiving upadacitinib.

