To address this gap, we aim to examine the immune response to the recombinant zoster vaccine Shingrix^®^ in Japanese patients with RA receiving upadacitinib. We assess immunogenicity at week 4 and RA flare ups to week 12 after the second Shingrix^®^ dose in patients receiving MTX (6–12 mg/week) monotherapy (Arm 1), upadacitinib (15 mg/day) monotherapy (Arm 2), and MTX (6–12 mg/week) + upadacitinib (15 mg/day) combination therapy (Arm 3). Immunogenicity and RA flares will be determined as previously described (immunogenicity [11] and RA flare [7,10]). In addition to humoral immune response (anti-gE-specific antibodies and anti-VZV-specific antibodies), cellular immune response (e.g., VZV-specific T-cell response) will be tested in this study, since the latter is a better surrogate marker for protection against herpes zoster [12,13,14]. Both humoral and cellular immunity have been reported to peak approximately 1 month after the second shot of the vaccine [15]; thus, the time point for the primary endpoint was set at 4 weeks after the second shot. In addition, the time points for secondary endpoints were set at 4 weeks after the first and second shots. Moreover, since recombinant zoster vaccine is associated with potential exacerbations or new onset of immune-mediated disease [16], not only disease activity of RA but also other adverse events will be carefully monitored.

The objective of this study is to investigate the immunogenicity and disease flares following recombinant zoster vaccination (Shingrix^®^) in Japanese patients with RA receiving MTX (6–12 mg/week) + upadacitinib (15 mg/day) combination therapy.

This is an exploratory, interventional, open-label, parallel triple-arm, prospective study. The three arms comprise the following regimens administered at patient registration:(1)MTX monotherapy (6–12 mg/week).(2)Upadacitinib monotherapy (15 mg/day).(3)MTX (6–12 mg/week) + upadacitinib (15 mg/day) (primary evaluation target) combination therapy.

All patients in the three groups will receive two intramuscular injections of the recombinant zoster vaccine at 8-week intervals. It should be noted that MTX can be used up to 16 mg/week in Japan. However, the dose indicated in the study was based on the typical dose administered in most institutions (6–12 mg/week) [17,18]. The upadacitinib dose (15 mg/day) was set as the approved dose.

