## 3. Interventions

### 3.1. Explanation for the Choice of Comparators

The study will employ two comparator groups to assess the effect of the recombinant zoster vaccine (Shingrix^®^): MTX monotherapy (6–12 mg/week) and upadacitinib monotherapy (15 mg/day).

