## 4. Outcomes

### 4.1. Primary Endpoint

Proportion of participants with positive anti-gE antibodies at 4 weeks after the second Shingrix^®^ dose.

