### 7.3. Secondary Endpoints

(1)Presence or absence of RA flares from enrollment to 12 weeks after the second Shingrix^®^ dose.

The numbers and proportions of patients with RA flares are summarized for each group.

(2)Proportion of positive anti-gE antibodies at 4 weeks after the first Shingrix^®^ dose.

The number and proportion of patients positive for anti-gE antibodies at 4 weeks after the first Shingrix^®^ dose will be summarized for each group. Evaluations will also be conducted after adjusting for confounders.

(3)Antibody titre of anti-gE antibodies at 4 weeks after the first and second Shingrix^®^ doses.

Means, standard deviations, medians, interquartile ranges, minimum values, maximum values, 95% confidence intervals, and numbers of missing values are described for each group.

(4)Proportion of gE-specific CD4+ T-cells at 4 weeks after the first and second Shingrix^®^ doses.

Means, standard deviations, medians, interquartile ranges, minimum values, maximum values, 95% confidence intervals, and numbers of missing values are described for each group.

(5)Antibody titer of VZV-specific antibodies at 4 weeks after first and second Shingrix^®^ doses.

Means, standard deviations, medians, interquartile ranges, minimum values, maximum values, 95% confidence intervals, and numbers of missing values are described for each group.

(6)Changes in RA disease activity.

Means, standard deviations, medians, interquartile ranges, minimum values, maximum values, 95% confidence intervals, and numbers of missing values are described for each group.

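### None of the three binary outcomes, the primary included, has a planned confidence interval, and no arm contrast or effect measure is named for the primary endpoint

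*Protocol article*

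**What the plan says.** Section 4.1 defines the primary endpoint as a binary outcome: "Proportion of participants with positive anti-gE antibodies at 4 weeks after the second" vaccine dose. Section 7.2 gives its whole analysis in one sentence, a tabulation by group of "The number and proportion of patients positive for anti-gE antibodies at 4 weeks after the second" dose.

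Section 7.3 then goes through the secondary endpoints one by one:

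- Item 1, RA flare: "The numbers and proportions of patients with RA flares are summarized for each group".
- Item 2, positivity after the first dose: "The number and proportion of patients positive for anti-gE antibodies at 4 weeks after the first" dose, by group, with the addition "Evaluations will also be conducted after adjusting for confounders".
- Items 3 to 6 (anti-gE titre, gE-specific CD4+ T-cells, VZV antibody titre, disease activity): a fixed list of summary statistics for each group that includes 95% confidence intervals.

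On comparison, the Introduction lists the combination arm (Arm 3) as "primary evaluation target) combination therapy". Section 3.1 says "The study will employ two comparator groups", namely methotrexate monotherapy and upadacitinib monotherapy. The Abstract says that "results will be compared in an exploratory manner". Section 7.5 adds a supplementary logistic regression adjusted for age, sex and disease severity. The covariate list may be changed while the anti-gE data are blinded.

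**The concern.** Section 7 specifies its output endpoint by endpoint and calls for confidence intervals four times, but not for the primary endpoint or the two other binary outcomes. Followed as written, the primary analysis yields three separate percentages with no statement of their precision and no estimate of how the combination arm differs from either comparator.

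This matters because the sample size in section 4.4 rests on feasibility, with no power or precision target. In such a study the interval is the main way to show what the data can and cannot exclude. The Introduction reports that two other JAK inhibitors partly attenuate the response to this vaccine, so the question of interest is whether the response is reduced and by how much. Three bare percentages do not answer it.

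**Working it through.** **1. The plan's own figure.** Section 4.4 gives 20 patients for each of the two upadacitinib groups, a 10% dropout rate and a target of 23 per group. 20 / (1 − 0.10) = 22.2, rounded up to 23, and 3 × 23 = 69, the total in the Abstract. The figure reproduces. I take 20 evaluable in the methotrexate arm as well, since its target is also 23.

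**2. Which outcomes have a stated interval.**

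| Outcome | Type | 95% CI stated |
|---|---|---|
| Primary: positivity after dose 2 (7.2) | binary | no |
| RA flare (7.3, item 1) | binary | no |
| Positivity after dose 1 (7.3, item 2) | binary | no |
| Anti-gE titre (item 3) | continuous | yes |
| gE-specific CD4+ T-cells (item 4) | continuous | yes |
| VZV antibody titre (item 5) | continuous | yes |
| Disease activity (item 6) | continuous | yes |

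The dividing line is binary versus continuous.

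**3. Precision of one arm.** The article gives no expected positivity rate, so the observed counts below are assumptions. The Wilson limits, with z = 1.96, are

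[p + z²/(2n) ± z·√(p(1 − p)/n + z²/(4n²))] / (1 + z²/n).

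For 16/20, the divisor is 1 + 3.84/20 = 1.192, the centre is (0.80 + 0.096)/1.192 = 0.752 and the half-width is 0.168, so the limits are 0.584 and 0.919.

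| Assumed result | Proportion | Wilson 95% CI | Exact 95% CI |
|---|---|---|---|
| 14/20 | 70% | 48.1–85.5% | 45.7–88.1% |
| 16/20 | 80% | 58.4–91.9% | 56.3–94.3% |
| 18/20 | 90% | 69.9–97.2% | 68.3–98.8% |
| 20/20 | 100% | 83.9–100% | 83.2–100% |

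**4. Precision of a difference.** With Wilson limits (l₁, u₁) and (l₂, u₂), the Newcombe interval for d = p₁ − p₂ is

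lower = d − √[(p₁ − l₁)² + (u₂ − p₂)²], upper = d + √[(u₁ − p₁)² + (p₂ − l₂)²].

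For 16/20 v 16/20: √[(0.800 − 0.584)² + (0.919 − 0.800)²] = √(0.0467 + 0.0142) = 0.247.

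| Assumed results | Difference (points) | Newcombe 95% CI (points) |
|---|---|---|
| 16/20 v 16/20 | 0 | −24.7 to +24.7 |
| 18/20 v 18/20 | 0 | −21.4 to +21.4 |
| 20/20 v 20/20 | 0 | −16.1 to +16.1 |
| 14/20 v 18/20 | −20 | −43.1 to +5.4 |
| 18/23 v 18/23 | 0 | −23.5 to +23.5 |

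Keeping all 23 enrolled patients changes little (last row). Only near 100% positivity in both arms does the interval become appreciably narrower.

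**5. Is a contrast named elsewhere?** The Abstract promises a comparison without saying of which arms or on what scale. Section 3.1 names both comparators and ranks neither. Section 7.5 names a model and covariates, but neither the outcome nor the arm contrast. Its reference to blinding of the anti-gE data implies an anti-gE outcome, but not at which time point. Section 7.3 attaches an adjusted evaluation to positivity after the first dose; section 7.2 attaches none to the primary endpoint.

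**The case against.** The strongest reply is that the plan is consistent with its declared design. The study is exploratory, its size is set by feasibility, and the Discussion acknowledges the small sample. Descriptive summaries suit that purpose. The choice of interval method is commonly left to an analysis plan, and one may exist. Section 7.2 does not exclude intervals. Section 7.5 also offers an evident vehicle for the promised comparison, one that deals with confounding, which a crude difference between non-randomised arms does not.

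Much of this stands. It limits the weight of the point, and it means that crude differences alone would be an inadequate remedy. It does not remove the point. A confidence interval is itself descriptive, and the article already uses it that way for four endpoints. Section 7.5 cannot stand in for a primary contrast while its outcome and arms are unnamed.

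Two stronger readings are tempting and not supported. A reader might infer that the primary endpoint alone is given weaker reporting, but RA flare and positivity after the first dose are treated identically. A reader might also infer that the authors plan to claim preserved immunogenicity from similar percentages. No section says so; that is a prediction about how results would be read.

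**Conclusion.** The point holds as a matter of reporting and specification. All three binary outcomes, including the primary, lack a stated interval while all four continuous ones have one. The article also promises a comparison centred on the combination arm without naming the contrast or the effect measure for the primary endpoint.

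Under assumed observed rates of 80% to 90% and 20 evaluable patients per arm, equal proportions leave differences of about 21 to 25 points either way unexcluded, and a 20-point shortfall (14/20 v 18/20) has an interval that includes zero. These rates are illustrative because the article states none. The intervals reflect sampling error only and say nothing about confounding between the arms. This should be changed, but it does not undermine the design.

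**What to change.** **Sections 7.2 and 7.3, items 1 and 2.** For each arm, report the proportion with a Wilson or exact 95% confidence interval. Add combination minus methotrexate and combination minus upadacitinib, each with a Newcombe 95% interval. Rank neither contrast, since the article does not, and label both as exploratory estimation without testing. State that similar percentages are not evidence of equivalence.

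**Section 7.5.** Name the primary endpoint as the outcome of the logistic regression. Give the same two arm contrasts, adjusted for the listed confounders, with the effect measure stated and 95% intervals. This is needed because patients enter the arms on their existing therapy and are not randomised.

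**Cost.** Wording only: no added patients, visits or samples. The wide intervals become visible. The adjusted model may be fragile: at 80% to 90% positivity, 60 evaluable patients would include only 6 to 12 negatives (60 × 0.10 to 60 × 0.20), against at least five coefficients (two for arm, plus age, sex and severity). The adjusted results should therefore be read beside the crude intervals.

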### 7.3. Secondary Endpoints

(1)Presence or absence of RA flares from enrollment to 12 weeks after the second Shingrix^®^ dose.

The numbers and proportions of patients with RA flares are summarized for each group.

(2)Proportion of positive anti-gE antibodies at 4 weeks after the first Shingrix^®^ dose.

The number and proportion of patients positive for anti-gE antibodies at 4 weeks after the first Shingrix^®^ dose will be summarized for each group. Evaluations will also be conducted after adjusting for confounders.

(3)Antibody titre of anti-gE antibodies at 4 weeks after the first and second Shingrix^®^ doses.

Means, standard deviations, medians, interquartile ranges, minimum values, maximum values, 95% confidence intervals, and numbers of missing values are described for each group.

(4)Proportion of gE-specific CD4+ T-cells at 4 weeks after the first and second Shingrix^®^ doses.

Means, standard deviations, medians, interquartile ranges, minimum values, maximum values, 95% confidence intervals, and numbers of missing values are described for each group.

(5)Antibody titer of VZV-specific antibodies at 4 weeks after first and second Shingrix^®^ doses.

Means, standard deviations, medians, interquartile ranges, minimum values, maximum values, 95% confidence intervals, and numbers of missing values are described for each group.

(6)Changes in RA disease activity.

Means, standard deviations, medians, interquartile ranges, minimum values, maximum values, 95% confidence intervals, and numbers of missing values are described for each group.

### 7.4. Interim Analyses

Interim analyses will not be conducted in this study.

### 7.5. Methods for Additional Analyses (e.g., Subgroup Analyses)

Multivariate logistic regression with adjustments for confounding factors (age, sex, and disease severity) will be performed as a supplementary analysis. The study subject background will be reviewed, and the addition or exclusion of confounding factors will be allowed under blinding of anti-gE antibody data.

### 7.6. Methods in Analysis to Handle Protocol Non-Adherence and Any Statistical Methods to Handle Missing Data

#### 7.6.1. Handling of Patients Enrolled in the Study

In case of a query, the handling of patients will be decided after a discussion between the principal investigator, statistical analyst, and other relevant departments. Decisions regarding case handling are also recorded.

#### 7.6.2. Handling of Outliers or Abnormal Values

If it is an obvious error, values will be reconsidered or remeasured; otherwise, no changes will be made to these values.

#### 7.6.3. Handling of Missing Values

Omissions in the EDC system are monitored and compensated, if necessary. No multiple imputations will be performed. Missing values outside the EDC system can be compensated at the next visit, if possible.

### 7.7. Plans to Give Access to the Full Protocol, Participant Level-Data, and Statistical Code

Access to the protocol and other materials related to the study will be provided to the research subjects upon request.

## 8. Oversight and Monitoring

### 8.1. Composition of the Coordinating Centre and Trial Steering Committee

The Center for clinical research and innovation (CCRI) at Osaka Metropolitan University Hospital will assist in protocol development, EDC system setup, statistical analysis, monitoring, data management, and manuscript editing. The principal investigator will maintain contact with the study participants at least once a month.

### 8.2. Composition of the Data Monitoring Committee, Its Role and Reporting Structure

For quality control, the principal investigator will prepare a written procedure for monitoring, which will be approved by the accredited clinical research review committee. Moreover, the principal investigator will designate a person in charge of monitoring, independent of the sponsor and competing interests. Throughout the study period, the person in charge of monitoring will confirm if the study is being conducted in accordance to the monitoring protocol, as well as the latest guidelines and regulatory requirements (e.g., Clinical Research Act, enforcement regulations). Furthermore, this person will report the results to the principal investigator in accordance with the monitoring protocol. In addition, any personal information of the research participants obtained from monitoring should not be divulged.

### 8.3. Adverse Event Reporting and Harms

The time of onset/disappearance, treatment, outcome, severity, relationship with study drugs, and predictability of adverse events will be documented in the medical records and EDC system. All adverse events occurring from study drug initiation to the end of the observation period will be recorded.

#### 8.3.1. Definition of Adverse Events

An adverse event is defined as any unfavourable symptom, sign, disease, or abnormal laboratory test value that occurs in a patient after administration of the study drug, regardless of the causal relationship.

#### 8.3.2. Evaluation for Severity

The severity of adverse events is evaluated according to the following criteria:(1)Mild: when administration can be continued without treatment.(2)Moderate: when administration can be continued with some kind of treatment.(3)Severe: when discontinuation is required for the patient.

#### 8.3.3. Evaluation for Seriousness

Seriousness is determined according to the following criteria:
(1)Serious
1.Death.2.A condition that may lead to death.3.A condition that requires hospitalization at a medical institution or an extension of hospitalization for treatment.4.Disability.5.A condition that may lead to disability.6.A condition that is serious according to criteria 1–5.7.Congenital diseases or abnormalities in later generations.

Note: Hospitalizations scheduled before study participation, hospitalizations for examination purposes, and extension of the hospitalization period are not considered serious adverse events.

(2)Non-Serious

Anything other than “serious” aforementioned events.

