#### 8.3.4. Illness Related to the Study

(1)Definition of illness

Disease, disability, death, infectious disease, or abnormal laboratory test values and symptoms suspected to be caused by the implementation of the study are defined as illnesses. Moreover, a causal relationship between the study drug used and the study procedure will be determined by the principal investigator and co-investigator.

(2)Predictability

Events that cannot be predicted from the package insert (container/encapsulation) of the study drug and the precautions written in the interview form are categorized as “unknown,” whereas those that are listed and can be predicted are categorized as “known”.

(3)Causality

In this study, causality is defined as a causal relationship that cannot be denied, based on the judgement of the principal investigator and co-investigator. When deciding, they will consider not only the temporal relationship with the initiation of interventional but also the course of underlying diseases, complications, concomitant medications, study procedures, accidents, and other environmental factors. Causality is judged and recorded throughout the study period.

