#### 8.3.5. Subjects and Reporting Period for Reporting Illness

If the investigator becomes aware of a disease or other matters that requires reporting within the time limit listed in the table below, the principal investigator reports it to the administrator of the medical institution and an accredited clinical research review board within the specified period. Additionally, this information will be provided to manufacturers and distributors of pharmaceuticals (Table 2).

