**Figure 2 jcm-13-07321-f002:**
[figure not shown]
Sample size explanation. IC: informed consent, MTX: methotrexate, RA: rheumatoid arthritis, UPA: upadacitinib.

**Table 1 jcm-13-07321-t001:** Participant timeline.

	Before Enrollment	At Enrollment	Week 4	Week 8	Week 12	Week 20
Visit	0	1	2	3	4	5
Allowance			+1 week	+2 week	+3 week * 1	−2~+4 week * 2
Informed consent		X				
Eligibility screen		X				
Shingrix^®^ injection		X		X		
Disease activity of RA	X	X	X	X	X	X
Assessment of adverse events		X	X	X	X	X
Blood tests * 3 Urine tests * 4 Serum storage	X	X	X	X	X	X
Immunogenicity * 5		X	X		X	
Additional blood collection		X	X		X	
Confirmation of concomitant drug	X	X	X	X	X	X
RA flare						X

* 1: 4 weeks + 1 week after the second Shingrix^®^ dose; * 2: 12 weeks ± 2 weeks after the second Shingrix^®^ dose; * 3: Blood tests include white blood cell count, red blood cell count, haemoglobin, platelet count, albumin, aspartate aminotransferase (AST), alanine aminotransferase (ALT), creatinine, blood urea nitrogen (BUN), CRP, and rheumatoid factor (RF); * 4 Urine test results include urine protein and occult blood; * 5 Immunogenicity evaluation includes anti-gE antibody, gE-specific CD4+ T-cells, and VZV-specific antibodies.

**Table 2 jcm-13-07321-t002:** Type of report.

			Regional Bureau of Health and Welfare	Accredited Clinical Research Review Board	
Type of Report			Regular Report	On-Time Report	Regular Report
Pharmaceuticals	Known	Death	〇	15 days	〇
		Serious condition other than death	〇	15 days	〇
		Non-serious	〇	―	〇
	Unknown	Death	〇	15 days	〇
		Serious condition other than death	〇	30 days	〇
		Non-serious	〇	―	〇
Infection	Known	Death/Serious	〇	15 days	〇
		Non-serious	〇	15 days	〇
	Unknown	Death/Serious	〇	15 days	〇
		Non-serious	〇	―	〇

〇 means required, and ― means not required.

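### Criterion 3 and the Note in Section 8.3.3 disagree on extended hospital stays, so a study-related event that prolongs a stay begun for another reason could lose its on-time report

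*Protocol article*

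**What the plan says.** Section 8.3.3 of the protocol article lists seven criteria for a serious event. Criterion 3 is "A condition that requires hospitalization at a medical institution or an extension of hospitalization for treatment". Criterion 6 covers a condition that is serious under criteria 1–5 and adds no wording of its own.

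A Note follows the list. It first removes admissions arranged before the patient joined the study, and then continues: "hospitalizations for examination purposes, and extension of the hospitalization period are not considered serious adverse events". The non-serious class is whatever remains: "Anything other than “serious” aforementioned events".

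Two later sections make this classification matter. Section 8.3.4 fixes which events enter the reporting rule; among others, "symptoms suspected to be caused by the implementation of the study are defined as illnesses". Section 8.3.5 then has the principal investigator report to the head of the institution and to the review board any matter that "requires reporting within the time limit listed in the table below", which is Table 2. There, the row "Serious condition other than death" carries a dated on-time report, while most non-serious rows carry a dash. The legend reads "〇 means required, and ― means not required".

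**The concern.** A stay lengthened in order to treat an adverse event fits criterion 3 and also fits the third item of the Note. Nothing in the section says which governs. A note placed after a list of criteria is naturally read as an exception to them, so an investigator acting in good faith could record such an event as non-serious.

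Criterion 6 sits where one would expect a category for other important conditions, and such a category could have recovered the event. As worded, it refers only to what criteria 1–5 already make serious, so it recovers nothing.

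What is at stake is the timing of safety reports. Seriousness is one of the factors that decide whether an event goes to the review board by a fixed date or only in the regular report.

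**Working it through.** The document gives no figure to reproduce, and the point rests on no calculation. The check sets the rules beside each other and then follows the consequence through Table 2.

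**Step 1: four kinds of stay under the two rules of Section 8.3.3.**

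| Situation | Criterion 3 | Note, as written |
|---|---|---|
| An adverse event causes the admission | Serious (first limb) | The admission is not excluded |
| Unplanned stay for another reason, prolonged to treat a new event | Serious (second limb) | Not serious |
| Planned or examination stay, prolonged to treat a new event | Serious (second limb) | Not serious |
| Planned or examination stay, prolonged for a non-medical reason | Not met | Not serious |

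The rules collide in rows two and three. In row one the event is already serious because of the admission, and a later extension does not change that.

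**Step 2: can another criterion settle rows two and three?** Criteria 1, 2, 4, 5 and 7 (death, risk of death, disability, risk of disability, congenital effects) stand on their own, so an event that meets one of them stays serious. Criterion 6 adds nothing to criteria 1–5. An event that meets none of the others depends on criterion 3 alone, and that is where the Note bites.

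**Step 3: does the event enter the reporting rule?** Only if it is suspected to be study-related (Section 8.3.4). Otherwise no on-time report was due.

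**Step 4: on-time report in Table 2 for a non-fatal event that moves from serious to non-serious.**

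| Category | Classed serious | Classed non-serious | On-time report |
|---|---|---|---|
| Pharmaceutical, known | 15 days | ― | Lost |
| Pharmaceutical, unknown | 30 days | ― | Lost |
| Infection, known | 15 days | 15 days | Kept |
| Infection, unknown | 15 days | ― | Lost |

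The on-time report is lost in 3 of 4 categories. The regular report is required in all eight cells, so the event would still reach the review board, but without a fixed deadline.

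**The case against.** The best defence is that the section can be read coherently. Criterion 3 speaks of extensions for treatment. The first two items of the Note are admissions that no adverse event caused, and the third can be read in their company as the lengthening of such stays where no treatment is needed. The article is also condensed, and the full protocol may be worded more tightly.

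This is plausible as intent, but it is not what the text says. The extension is a separate item with no qualifier. Limiting it to planned and examination stays clears row two of the first table but leaves row three under both rules. The conflict goes only if the reader also supplies the absence of a treatment need, and that is the limit the Note lacks. Nor does this fault something left out of a condensed article: the article states the rule, and states it in two ways.

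The defence is right about reach. Four conditions must hold together: the patient is already in hospital for another reason, the event lengthens the stay, no other criterion is met, and a link to the study is suspected. A reader might infer that sites will class any treated, prolonged admission as non-serious, or that every such event loses its dated report. The documents support neither. Admissions caused by an adverse event are untouched, events unrelated to the study are outside the rule, and a known infection keeps its deadline.

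On criterion 6, its author probably meant conditions of comparable weight, and criteria 2 and 5 already reach many important events outside hospital. It would go too far to say that such events cannot be captured. What stands is that criterion 6 as written is circular.

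**Conclusion.** The contradiction stands on the face of Section 8.3.3, and the wording should be corrected. Its reach is narrow: an adverse event that prolongs a stay begun for another reason and meets no other seriousness criterion could be classed as non-serious. If it is suspected to be study-related, the loss is a report due in 15 or 30 days, in three of the four non-fatal categories of Table 2. This assumes an investigator who gives the Note precedence over criterion 3, which the text permits but does not require. The document gives no basis for estimating how often this would happen.

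A reader might want to size the problem as a shift in an arm's serious-event rate, for example one patient in 20, or 5 percentage points. That figure should not be used. The safety set in Section 7.1.3 is everyone vaccinated at least once; at the target of 23 per group, one event is 1/23 = 4.3 points. More to the point, no serious-event rate is among the listed endpoints, and the same arithmetic applies to any single event. The primary endpoint and its analysis are unaffected. Section 3.3.1 also mentions serious adverse events among the reasons for discontinuation, but that decision rests on the investigator's judgement, so no effect there is claimed.

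**What to change.** Make three changes:

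- Reconcile the Note with criterion 3. Limit the Note to stays planned before participation or made for examination, and to extensions that no adverse event caused. State that a stay lengthened to treat an adverse event falls under criterion 3.
- Reword criterion 6 to cover conditions comparable in seriousness to those in criteria 1–5.
- Re-check the events recorded as non-serious that involved a prolonged stay, and reclassify and report them where the clarified rule requires it.

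The cost is a short amendment, which needs committee review under Section 8.5, a brief look-back through the recorded events, and possibly a few more on-time reports. Section 10 gives the trial as recruiting, with completion estimated for 31 March 2026. The look-back remains useful after enrollment closes, because it also corrects the final safety record.
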